### Aims

The primary objective of our study was to compare the effect of extended-release isosorbide mononitrate on clinical PP with that of a placebo, in addition to the standard treatment, in patients over 65 with refractory ISH after 3 months of treatment.

The secondary goals were as follows:

1. To quantify the effect of extended-release isosorbide mononitrate on vascular function (estimated using CBP, AI, and PWV).

2. To evaluate the safety profile by estimating the frequency, type, and severity of adverse events and the percentage of patients who had to withdraw from the study because of adverse events, in particular headache and orthostatic hypotension.

3. To determine the percentage of patients who reach clinical SBP <140 mmHg in both treatments groups.

4. To determine the percentage of patients who reach a 24-hour mean SBP <130 mmHg (measured using ambulatory blood pressure monitoring (ABPM)) in both treatment groups.

5. To measure the change in PP using ABPM.

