### The study began in January 2013 and is ongoing

#### Participants

The study population comprises patients aged ≥65 years of both genders attended at primary care centers or at the Hypertension Unit of Hospital La Princesa. All patients give their written informed consent to participate in the study. Patients are included if they meet all the inclusion criteria and none of the exclusion criteria. Table 1 shows the inclusion and exclusion criteria .

**Table 1 T1:** Inclusion and exclusion criteria

**Inclusion criteria**	**Exclusion criteria**
Aged 65 or over	Current treatment with nitrates, intolerance to them or contraindication to their use
Refractory ISH: SBP ≥140 mmHg and DBP <90 mmHg and SBP in ABPM ≥130 mmHg, despite treatment with three drugs at maximum dosage, one of them diuretic, during at least one month before the start	Concomitant treatment with phosphodiesterase 5 inhibitors
	SBP ≥180 mmHg
Good adherence to treatment, defined as a good response to all questions of Morisky-Green’s test	Permanent atrial fibrillation
	Secondary hypertension
Life expectancy greater than 1 year	Congestive heart failure, grade III-IV NYHA
Signing the informed consent	Chronic kidney disease with glomerular filtration rate ≤30 ml/min, estimated by MDRD
Ability to understand study procedures and to comply with them for the entire length of the study	
	Liver insufficiency
	Active cancer
	Anemia ≤8 g/dl
	Simultaneous participation in another clinical trial
	Not signing the informed consent
	Any other circumstance that, according to the research criteria, advises against the inclusion to the study

Patients are included if they meet all the inclusion criteria and none of the exclusion criteria.

ABPM: ambulatory blood pressure monitoring, DBP: diastolic blood pressure, ISH: isolated systolic hypertension, NYHA: New York heart association, MDRD: modification of diet in renal disease, SBP: systolic blood pressure.

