#### Statistical analysis

The statistical analysis will comprise the following parts:

1. In descriptive analysis of the sample, quantitative variables will be expressed as measures of central tendency (mean or median) and dispersion (standard deviation or interquartile range) for symmetrical distributions; normality will be tested using Kolmogorov-Smirnov test. Appropriate transformations will be applied in cases of a non-normal distribution. Qualitative variables will be expressed as proportions with their standard error.

2. Baseline characteristics, especially those that could influence the results, will be compared using the *t* test or Mann–Whitney test for quantitative variables and the Pearson chi-squared or Fisher exact test for qualitative variables. The main variables that could influence the result of this study at initiation are age, PP, SBP, and DBP. In the case of inequality, these factors will be treated as confounding variables in the final efficacy analysis.

3. The differences between the means and their confidence interval (CI), or the median ratio and their CI, will be used as the main measure of the effect. The relative risk, absolute risk reduction, and relative risk reduction will be used as a measure of the effect for the qualitative variables. A 95% CI will be calculated for all estimations.

4. To control for possible confounding variables, linear models or linear regression will be applied for dependent quantitative variables and logistic regression models for dependent qualitative variables.

5. In all the analyses, the null hypothesis tested will be the lack of effect (difference of means = 0, RR = 1) between the experimental and the control groups. Missing data will be processed using a sensitivity analysis.

6. As this is a two-arm, placebo-controlled, parallel study, no subgroups will be analyzed to measure secondary endpoints and no interim analysis will be performed.

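### Adjusted blood-pressure-control results would come out of logistic regression as odds ratios, whereas the plan declares relative risk and absolute risk reduction as its measures

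*Protocol article*

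**What the plan says.** All the relevant text is in the Protocol article.

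- **Outcomes.** Secondary goals 3 and 4 (Aims) are binary: "To determine the percentage of patients who reach clinical SBP <140 mmHg in both treatments groups" and "To determine the percentage of patients who reach a 24-hour mean SBP <130 mmHg". The section Evaluation of effectiveness counts both as secondary efficacy.
- **Effect measure** (Statistical analysis, item 3): "The relative risk, absolute risk reduction, and relative risk reduction will be used as a measure of the effect for the qualitative variables". The same item promises a 95% CI for every estimate.
- **Adjustment model** (item 4): "linear models or linear regression will be applied for dependent quantitative variables and logistic regression models for dependent qualitative variables". No other model is named for binary outcomes.
- **Null hypothesis** (item 5): "In all the analyses, the null hypothesis tested will be the lack of effect (difference of means = 0, RR = 1" for the comparison of the two groups.
- **When adjustment applies** (item 2, on age, PP, SBP and DBP): "In the case of inequality, these factors will be treated as confounding variables in the final efficacy analysis".
- **Status at entry** (Table 1): "Refractory ISH: SBP ≥140 mmHg and DBP <90 mmHg and SBP in ABPM ≥130 mmHg", so no patient is controlled on either outcome at baseline. No control rate at 12 weeks is given for either arm.

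**The concern.** For continuous outcomes the plan is coherent: the difference of means in item 3 is the treatment coefficient of the linear model in item 4. For binary outcomes the two items do not meet. Item 3 names three measures built on risks, while the model in item 4 directly yields a conditional odds ratio, which is none of the three.

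The conditional odds ratio differs from an RR in two ways. It lies further from 1 than the RR, increasingly so as the outcome becomes more frequent. It also changes when a prognostic covariate is added, even if that covariate is balanced between arms.

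What is at stake is the reporting of the two control outcomes. With balanced baselines, the result would be an RR and a risk difference. With a baseline imbalance, the final result would come from the logistic model, on another scale. A baseline check would then decide the scale of the reported effect, and a reader could take an odds ratio for a relative risk.

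**Working it through.** **The plan's own figures.** No rate, RR or odds ratio is stated for any binary outcome, so there is nothing to reproduce on this point. The one design figure, 64 evaluable per group for pulse pressure, reproduces (difference 8, SD 16, two-sided 5%, 80% power, t test: 63.8, rounded up to 64) and has no bearing here.

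**Step 1: odds ratio against RR, no covariates.** The placebo control rate p0 and a true RR of 1.5 are assumptions. With p1 = 1.5 × p0,

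OR = [p1/(1 − p1)] / [p0/(1 − p0)].

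For example, at p0 = 0.20: p1 = 0.30 and OR = (0.30/0.70)/(0.20/0.80) = 0.4286/0.25 = 1.71.

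| Placebo control rate | Active control rate | RR | OR | OR/RR | Risk difference |
|---|---|---|---|---|---|
| 5% | 7.5% | 1.5 | 1.54 | 1.03 | 2.5 points |
| 10% | 15% | 1.5 | 1.59 | 1.06 | 5 points |
| 20% | 30% | 1.5 | 1.71 | 1.14 | 10 points |
| 30% | 45% | 1.5 | 1.91 | 1.27 | 15 points |
| 40% | 60% | 1.5 | 2.25 | 1.50 | 20 points |

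The gap is small at placebo rates of about 10% or less and material from about 20% upward.

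**Step 2: effect of adjusting, and whether the declared measures can be recovered.** For each of four placebo rates, 400,000 patients were simulated with 1:1 random allocation, true RR 1.5, and one standard normal covariate with a log-odds slope of −1, independent of treatment. A logistic model with treatment and covariate was fitted. It was then standardised: predict each patient's probability of control under active and under placebo, average each set, and take the ratio (RR) and the difference (RD).

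| Placebo rate | OR without covariate (step 1) | Conditional OR | Standardised RR | Standardised RD (true) |
|---|---|---|---|---|
| 10% | 1.59 | 1.67 | 1.49 | 0.050 (0.05) |
| 20% | 1.71 | 1.90 | 1.51 | 0.101 (0.10) |
| 30% | 1.91 | 2.16 | 1.50 | 0.148 (0.15) |
| 40% | 2.25 | 2.68 | 1.50 | 0.201 (0.20) |

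The conditional odds ratio moves further from 1 although there is no confounding. The same fitted model nevertheless returns the declared measures once it is standardised.

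**Step 3: the null hypothesis.** In a logistic model without treatment-by-covariate interaction, a treatment coefficient of zero gives every patient the same predicted probability under both arms. The standardised RR is then 1 and the risk difference 0. OR = 1 and RR = 1 are the same null, so item 5 is not breached.

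**Step 4: how often this matters.** Item 2 does not define inequality. If it meant p < 0.05 on any of the four named factors (an assumption), chance alone would trigger adjustment in about 5% of trials if the four tests moved together, and in 1 − 0.95⁴ = 0.185, about 19%, if they were independent.

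**The case against.** The strongest reply is that nothing in the text is false. A model is not an effect measure. Item 4 says how confounding will be handled, item 3 says what will be reported, and step 2 shows that the model in item 4 can deliver the measures in item 3. The missing piece is one post-estimation step, which a journal article may leave to a fuller document. The outcomes are secondary, and adjustment is conditional.

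Most of this stands, and it is why the point is minor. It does not remove the point. The article chose to fix both the measure and the model, and as written the direct result of the one is not the other.

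A reader might also infer more than the documents support:

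- *That the plan will exaggerate the effect on control.* An odds ratio is a different measure; it overstates an RR only if read as one. The article nowhere says that an odds ratio will be reported, and names only risk-based measures.
- *That blood-pressure control is a common outcome here.* No control rate is given. All patients are uncontrolled at entry despite three drugs, so the rate could be low, and at 5% to 10% the gap in step 1 is slight.
- *That logistic regression is the wrong model or the test is invalid.* Steps 2 and 3 show otherwise.

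**Conclusion.** The mismatch is real and minor. As written, an adjusted result for the two secondary control outcomes would not be on the scale that item 3 declares, because the only adjustment model named gives a conditional odds ratio and no conversion is stated.

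For an assumed RR of 1.5, the odds ratio exceeds the RR by a factor of 1.03 at a 5% placebo control rate, rising to 1.50 at 40%. Adjustment for a prognostic covariate widens the gap further under the simulated covariate strength. All these figures rest on assumed rates. The numerical difference becomes an error of interpretation only if an odds ratio is read as a relative risk.

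The hypothesis test, the unadjusted RR and risk difference, and the primary pulse-pressure analysis are unaffected.

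**What to change.** Add a sentence or two to the analysis plan:

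- Keep logistic regression for the two control outcomes, with prespecified adjustment for the matching baseline SBP: clinic SBP for the clinic outcome, ABPM SBP for the 24-hour outcome. For these outcomes this replaces the trigger on observed inequality.
- Report the adjusted risk difference and risk ratio by marginal standardisation of that model, with delta-method or bootstrap 95% CIs. A modified Poisson model with robust standard errors is an alternative for the risk ratio.
- Define the event as control achieved, and use the terms risk difference and risk ratio. The outcome is favourable, so a reduction measure computed on it turns negative when the drug works: at 20% against 30%, the relative risk reduction is 1 − 1.5 = −50%.

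The cost is this wording and a few lines of code. No new data are needed, since clinic and ambulatory pressures are already recorded at baseline (Variables, items 5 and 6). The article describes the trial as still recruiting, so at that stage the change could be made before unblinding.

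One caution is that control may prove rare. At 5% against 7.5% with 77 per group, about 77 × 0.05 + 77 × 0.075 = 9.6 events are expected in total. The single baseline covariate is then as much as the model should carry, and the intervals need care.

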## Discussion

ISH remains difficult to control in many cases, despite the availability of various types of appropriate medication; however, most are able to reduce SBP, albeit with a considerable associated reduction in DBP. The consequent severe side effects, such as reduced coronary perfusion and orthostatic hypotension, limit treatment options.

Hypertension continues to be the most important cardiovascular risk factor today, and cardiovascular illnesses are the main cause of death in developed countries, especially among people over 65.

The results of our trial should demonstrate whether treatment with isosorbide mononitrate improves not only control of arterial pressure, but also vascular function in patients with refractory ISH. If our hypotheses are proved, a clinical trial with morbidity and mortality as the main end-points would be justified. Such a trial could also be used to investigate the long-term effects of this drug.

Few clinical trials have been carried out to test oral nitrates in patients with ISH, even though these agents seem to be effective and have been used over long periods in the treatment of other illnesses, such as ischemic heart disease, hypertensive emergency, or acute lung edema.

Our trial is performed on a collaborative basis between the hospital (center for recruitment and vascular function tests) and the primary care center, because most of these patients have their main contact with the health service through their primary care physicians. A collaboration of this type makes it easier to reach patients and provides more robust results with greater external validity.

Our study is subject to three limitations. First, potentially high loss to follow-up because of non-fatal side effects; however, this is compensated for, as it was taken into account in the sample size calculation. Second, in the long term, patients could develop tolerance to nitrates, although this was not demonstrated in any of the trials we reviewed. Finally, our trial was not designed to demonstrate reductions in morbidity and mortality; rather, our main objective was to evaluate tolerance and effects on some intermediate variables.

In conclusion, treatment of ISH with extended-release isosorbide mononitrate could improve control of SBP with minimal side effects, thus helping to reduce the morbidity and mortality of the disease.

## Trial status

The trial is in the recruitment phase.

## Abbreviations

AE: Adverse event; AI: Augmentation index; AR: Adverse reaction; BP: Blood pressure; CBP: Central blood pressure; CI: Confidence interval; CRF: Case report form; DBP: Diastolic blood pressure; ISH: Isolated systolic hypertension; NO: Nitric oxide; PP: Pulse pressure; PWV: Pulse wave velocity; SBP: Systolic blood pressure.
